#### Drop-out, feasibility and motivational processes

Unfortunately, drop-out rates are quite high in treatment of obesity [132]. Therefore, increasing the motivation is important at the start of treatment, which will be emphasized during every EuREKA session. Moreover, to raise the motivation in the current study, participants in both the intervention and control group will receive a cinema voucher after completing the stress paradigm before (T1) and after the intervention (T2). Additionally, after every EuREKA session, the children in the intervention group will receive a little incentive, adjusted to the content of that particular EuREKA session. To test the feasibility of the ER training, after every session, the trainers and the participants will score the different components of the training on VAS (0–100 mm). Both the content of the training and the features of the session (e.g., group safety, attitude of the trainer) will be assessed. These insights aim to help understanding the drop-out and to improve the adherence rates [133]. Moreover, also the treatment integrity of the EuREKA training will be evaluated. Therefore, all sessions will be recorded and scored on VAS (0–100 mm) by independent raters.

### Data analysis

#### Sample size

To detect a clinically relevant treatment effect in both primary and secondary treatment outcomes, the power analysis was conducted on the AdjBMI index [80]. To detect a minimally important difference in the in AdjBMI-index (− 0.5 BMI points), a power analysis showed that 63 participants in every condition are necessary to obtain a power of 80% at a significance level of .05. As drop-out rates are high in inpatient treatment centers [132], we will include 10% more participants. This calculation leads to the inclusion of 70 participants in both the intervention and control condition.

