### Study design

The study design concerns a two-arm randomized controlled trial, evaluating the effects of an emotion regulation training intervention versus a care-as-usual control group. Assessments in the two conditions are planned at four time points: after recruitment (T0), before the start of the intervention (T1), after the end of the intervention (T2), and at 6-months’ follow-up (T3). Primary outcome measures are emotion regulation and eating behavior, more specifically emotional eating. As secondary outcome measures, (1) weight change, (2) psychological well-being, and (3) sleep quality will be taken into account.

After giving informed consent (T0), participants and their parents will fill out questionnaires assessing the psychological well-being, ER capacities, and perceived stress of the child (parent- and self-report), which will be used for descriptive purposes or as covariates. Next, before the start of the intervention (T1), at the end of the intervention (T2), and at 6 months’ follow-up (T3), participants will fill out questionnaires on their psychological well-being, sleep quality, ER capacities, eating behavior, and perceived stress level, and they will participate in a stress paradigm. On top, at T1, the participants will also complete the Standard Progressive Matrices test to determine their overall cognitive ability. Parents of the participants will be asked again to fill out questionnaires on the psychological well-being and the eating behavior of their child at T2 and T3. Moreover, the participants in the intervention condition will be asked to fill out a diary three times a week on their stress level, affect, ER capacities, and emotional eating behavior between the ER training sessions. Filling out a diary enables a more momentary inspection on the relationship between the stress level, ER capacities, and emotional eating behavior in the naturalistic environment of the participants.

The eligibility, allocation, and assessments are illustrated in Figs. 2 and 3.

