### Secondary outcome measures

#### Weight index and related metabolic parameters

##### Adjusted Body Mass Index (AdjBMI)

The Adjusted Body Mass Index (AdjBMI) will be used to objectify the weight index of the participants. This means that the BMI will be calculated and based on normative Flemish data [122] expressed as percentage above the mean, according to age and gender. Cutoff criteria for childhood overweight and obesity, based on age and gender growth charts, are proposed by the International Obesity Task Force (IOTF). These criteria are 25 kg/m^2^ and 30 kg/m^2^, respectively [38].

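### The target difference of 0.5 BMI points is not in AdjBMI's unit; 63 per arm is the sample size for 0.5 SD, and the calculation does not cover the primary outcomes

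*Protocol article*

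**What the plan says.** The Sample size section of the protocol article gives the trial's only power calculation. It opens: "To detect a clinically relevant treatment effect in both primary and secondary treatment outcomes, the power analysis was conducted on the AdjBMI index". It then sets the minimally important difference and the resulting number: "0.5 BMI points), a power analysis showed that 63 participants in every condition are necessary to obtain a power of 80" per cent, at an alpha of .05. A 10% allowance for drop-out brings 63 to 70 per arm, 140 in all. No SD, test or sidedness is given.

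The section defining AdjBMI stands under the secondary outcomes. It says that BMI is "expressed as percentage above the mean, according to age and gender". The Study design section says: "Primary outcome measures are emotion regulation and eating behavior, more specifically emotional eating". It lists weight change among the secondary outcomes.

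The Analytical plan specifies mixed models adjusted for baseline. The Background reports an effect of earlier multidisciplinary treatment on BMI of 0.5 SD.

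**The concern.** Two statements in the article do not fit together. The difference is expressed in BMI points, but the index on which it is to be detected is a percentage relative to a norm. A sample size cannot be computed from an absolute difference without an SD, and none is given. A sample size was nevertheless obtained, so some value was used that the text does not state.

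The second problem is coverage. A difference in AdjBMI, in whatever absolute unit, carries no information about power on an emotion regulation questionnaire or an emotional eating scale. Only a standardised difference could carry over from one outcome to another, and the text does not state one.

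At stake is how the results will be read. If weight shows no difference, readers may take the trial to have excluded an effect of 0.5 points with reasonable certainty. If the number really rests on 0.5 SD, the effect that could be detected may be several times larger. The primary outcomes, on which the trial will be judged, have no power statement of their own.

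**Working it through.** **Inputs from the article.** Difference 0.5 (labelled BMI points), alpha .05, power 80%, equal arms, 63 per arm before drop-out, 10% drop-out. Two-sided testing is assumed. It reproduces the stated number, whereas the one-sided version gives 50 to 51 per arm.

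**1. Reproducing 63 per arm.** For two means, n per arm = 2 × ((z for alpha + z for power) / d)², where d = difference / SD.

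With d = 0.5: 2 × ((1.960 + 0.842) / 0.5)² = 2 × 5.604² = 62.8, rounded up to 63.

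The exact t-test needs 63.8. With 63 per arm and d = 0.5, power is 80.1% (normal approximation) or 79.5% (t-test). The match requires SD = 1, so that 0.5 is in effect a standardised difference.

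**2. Drop-out.** 63 / 0.9 = 70. This reproduces.

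**3. What 0.5 points would need.** Solving the same formula for the SD at 63 per arm: SD = 0.5 / (2.802 × √(2/63)) = 1.00 point.

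The article gives no SD, so the SDs below are assumptions. The unit does not matter here as long as the difference and the SD share it.

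| Assumed SD (points) | d = 0.5 / SD | Power with 63 per arm (t-test) | n per arm for 80% |
|---|---|---|---|
| 1.0 | 0.50 | 80% | 63 |
| 1.5 | 0.33 | 46% | 142 |
| 2 | 0.25 | 29% | 252 |
| 5 | 0.10 | 9% | 1,570 |
| 10 | 0.05 | 6% | 6,280 |

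Put the other way, 63 per arm detects about half an SD with 80% power: about 1 point if the SD is 2, and about 5 points if it is 10.

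**4. Baseline adjustment.** The planned model adjusts for baseline, so the SD in the table should be read as the residual SD = raw SD × √(1 − r²), where r is the correlation between baseline and follow-up. The article gives no r. For 63 per arm to keep 80% power for 0.5 points, the raw SD may be at most:

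| Assumed r | 0 | 0.7 | 0.8 | 0.9 | 0.95 |
|---|---|---|---|---|---|
| Largest raw SD (points) | 1.0 | 1.4 | 1.7 | 2.3 | 3.2 |

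**5. Primary outcomes.** The article gives no difference, SD or standardised effect for emotion regulation or emotional eating, so nothing can be recomputed for them.

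**The case against.** The strongest reply is that nothing here shows the trial to be underpowered. The documents give no SD. The Sample size section cites a source for the AdjBMI index that is not at hand, and a condensed article may leave the SD to the full protocol. If the residual SD is about 1 point, 80% power for 0.5 points is correct. If 0.5 SD was meant and mislabelled, the number is also correct and the fault is one of wording. This reply stands. A reader might infer that the stated power is not delivered, or that the stated difference and the stated power cannot both hold, but the documents do not establish either.

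A reader might also argue that an SD near 1 point cannot be right for children admitted at 60% overweight or more. It does look small on a percentage scale. But an entry threshold does not give an SD, least of all a residual SD after baseline adjustment.

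The 0.5 SD in the Background invites the inference that this figure was copied and its unit changed. That is plausible but not shown. One figure is the effect of earlier multidisciplinary treatment, and the other is the difference sought between arms.

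Finally, the article remarks that "drop-out rates are quite high in treatment of obesity", which might prompt doubt about the 10% allowance. The documents give no drop-out rate to set against it, and 63 to 70 is computed correctly, so the allowance is not part of this point.

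The reply does not remove the conflict of units between two sections of the same article, nor does it support the claim to cover the primary outcomes. An SD held in another document would cure neither.

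**Conclusion.** The point holds in three parts.

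- **Unit.** The target difference is stated in a unit that AdjBMI, as defined in the same article, does not have. This needs no assumption.
- **Number.** 63 per arm supports a standardised difference of 0.5, two-sided. It supports an absolute 0.5 points only if the relevant SD is about 1 point. Beyond that, power falls quickly, to 46% at an SD of 1.5 and 29% at 2. These figures rest on assumed SDs and show the sensitivity; they do not estimate this trial's power.
- **Coverage.** The claim that the calculation serves the primary outcomes is unsupported, whatever the SD of AdjBMI is.

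The arithmetic itself reproduces, and the sample size need not be wrong. What is wrong as written is the description of what it can detect, and on which outcomes.

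**What to change.** In the Sample size section:

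1. Replace the difference in BMI points with: *a standardised difference of 0.5 (63 evaluable participants per arm, two-sided alpha .05, about 80% power for a single continuous outcome)*.
2. Give the equivalent of 0.5 SD in AdjBMI percentage points, with the SD, its source and, if used, the baseline correlation. If an absolute difference was meant instead, state its unit and SD, and restate the power that 63 per arm delivers.
3. Replace the claim to cover the primary outcomes with the standardised difference detectable on them. The article lists many measures under its primary outcomes and designates no single score for each domain, so the statement should be tied to whichever scores the authors designate.

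The cost is wording and one sourced SD. The target of 140 and the 10% drop-out allowance stay. The detectable weight difference may turn out less favourable than the present text suggests.

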#### Data storage

A research data management plan has been formulated, in which the collected data and data storage have been defined. The plan defines the location on the computer where the data is stored and who is responsible for the data.

#### Analytical plan

To solve the problems of noncompliance and missing outcomes, which are iterative complications in an RCT study, the intention-to-treat (ITT) principle will be used [69]. Multilevel analyses will be used to test the treatment effects, allowing handling of the missing and nested data from the two conditions (intervention versus control condition). More specifically, mixed models with fixed effects for condition (intervention versus control condition), time (immediately after intervention and 6 months’ follow-up), and their interaction, adjusted for baseline will be used.

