### Randomization

Stratified randomization is a two-stage process, used to control for the influence of covariates (baseline characteristics), in the randomization process [135]. In the current RCT study, both sex and age are identified as potential and important covariates. Therefore, separate blocks for each combination of the covariates will be generated (e.g., girls 10–12, boys 10–12, girls 13–14, and boys 13–14).

Participants who give consent to participate the study will be assigned to one of the four blocks.

Afterward, simple randomization to one of two conditions (e.g., experimental vs. care as usual condition) will be applied within each block at the individual level using dice [82]. The dice is thrown by the same researcher in all consecutive waves. Based on our a priori power calculations that 140 participants have to be included, we will recruit participants until each of the blocks has 35 participants.

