### Control variables

We will control for multiple variables that are known as important but without specific hypothesis regarding their effect on our outcome variables, e.g., eating disorders, medication use, smoking behavior, puberty state, alexithymia, and cognitive functioning. First, eating problems, such as loss of control and binge eating are often observed as comorbidities of obesity [59, 152], associated with more eating-related and internalizing psychopathology [59]. Second, medication use is associated with a lower heart rate variability [112]. Third, smoking behavior can be a confounder in the relation between stress and weight, as it is a maladaptive ER strategy. Moreover, smoking can influence the energy imbalance [154]. Fourth, obesity is associated with early puberty onset, initiated by high levels of leptin [131]. Besides, the pubertal development influences the stress regulation by changes in the cortisol axis [94]. Fifth, alexithymia is a construct referring to difficulties in identifying and describing emotions [136]. In addition, alexithymia is associated with difficulties in discriminating between different emotions [10] and with difficulties in coping with stressful events [115]. Sixth, cognitive functioning, more specifically executive functioning, is shown to play a role in the development and maintenance of overweight and obesity [57, 65].

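### The stated outcome model does not name sex and age, the two stratification factors, although dice allocation within strata does not balance the arms on them: a modest loss of precision

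*Protocol article*

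**What the plan says.** The Randomization section of the protocol article describes stratification as a way to control for covariates and states that "both sex and age are identified as potential and important covariates". The strata are "girls 10–12, boys 10–12, girls 13–14, and boys 13–14", with recruitment to 35 children in each. Simple randomisation to the two conditions "will be applied within each block at the individual level using dice".

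The Analytical plan specifies "mixed models with fixed effects for condition (intervention versus control condition), time (immediately after intervention and 6 months’ follow-up". The only further terms that it names come at the close of the same sentence: "and their interaction, adjusted for baseline will be used". Sex, age and stratum are not mentioned.

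Two other sections mention adjustment. Control variables gives "eating disorders, medication use, smoking behavior, puberty state, alexithymia, and cognitive functioning" as examples. Study design says of the T0 questionnaires on well-being, emotion regulation and perceived stress "which will be used for descriptive purposes or as covariates". Neither names sex or age.

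Two body-size outcomes already allow for age and sex: AdjBMI is "expressed as percentage above the mean, according to age and gender", and waist circumference is analysed as z-scores.

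**The concern.** A trial that stratifies by a factor would normally carry that factor into its analysis model. Here there is a second reason. Stratification controls a covariate at the design stage only if allocation within strata is restricted, for example by permuted blocks. Independent dice throws within a stratum leave the split to chance, so the stratification does not deliver the control that the Randomization section intends. The model is the remaining place to deliver it, and the stated model does not name the two factors.

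Two things are at stake. Outcome variance due to sex and age stays in the error term, which widens confidence intervals. A chance imbalance in sex or age, once it has occurred, also stays uncorrected in that trial's estimate.

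**Working it through.** **1. The plan's own figure.** Sample size gives 63 per arm for 80% power at the .05 level, and 70 per arm after a 10% allowance for drop-out. The SD is not stated. Assume SD = 1 and a two-sided test:

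n = 2 × (1.960 + 0.842)² / 0.5² = 62.8, so 63 per arm; 63 / 0.9 = 70.

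Both figures reproduce. Power at 63 per arm is Φ(0.5 × √(63/2) − 1.960) = Φ(2.806 − 1.960) = 80.1%. The 63 was derived for AdjBMI. It is used below only as a reference design for a 0.5 SD effect.

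**2. Imbalance under dice.** Inputs from Randomization: four strata of 35, each child allocated with probability 1/2. With 70 girls and 70 boys, the difference between arms in proportion of girls has SD of about √(0.25/70 + 0.25/70) = 0.085. A simulation of 100,000 allocations gave:

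- SD of the difference: 8.6 points
- 10 points or more: 27%
- 15 points or more: 8%
- at least one stratum split 12:23 or worse: 31%

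By symmetry the same figures hold for the two age groups.

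**3. Precision.** Let R² be the share of the variance left after baseline adjustment that sex and age explain. The documents give no value, so it is an assumed range. The standard error is multiplied by √(1 − R²), and power at 63 per arm becomes Φ(2.806/√(1 − R²) − 1.960).

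| R² (assumed) | Fall in SE | Power at 63 per arm | n per arm for 80% |
|---|---|---|---|
| 0 | 0 | 80.1% | 63 |
| 2% | 1.0% | 80.9% | 62 |
| 5% | 2.5% | 82.1% | 60 |
| 10% | 5.1% | 84.1% | 57 |
| 15% | 7.8% | 86.1% | 54 |

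**4. Simulation check.** The model was fitted with and without the two factors (n = 126, 4,000 trials per setting, one follow-up time). Sex and age effects are those remaining after baseline adjustment.

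| Effect of each factor | Power without | Power with |
|---|---|---|
| 0.2 SD | 79.4% | 79.2% |
| 0.3 SD | 79.4% | 80.1% |
| 0.5 SD | 79.6% | 84.2% |

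With no treatment effect, rejection was about 5% either way. The mean estimate matched the true effect either way. At 0.5 SD each, the SE fell from 0.175 to 0.164.

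**5. What the baseline score absorbs (illustration).** Assume a stable 0.5 SD sex difference at baseline and follow-up, and a within-sex correlation r between the two of 0.3 to 0.7. The sex effect left after adjustment is 0.5 × (1 − r), or 0.35 down to 0.15 SD. That is roughly 3% down to 1% of the residual variance. An equal age effect about doubles this, to roughly 2–6%. At 6%, power is Φ(2.806/√0.94 − 1.960) = 82.5%.

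**6. Shift from one imbalance.** The shift is the remaining sex effect times the difference in proportion of girls. At 15 points it is 0.15 × 0.15 = 0.02 SD to 0.35 × 0.15 = 0.05 SD. If a full 0.5 SD effect remained after adjustment, it would be 0.075 SD, still under half the simulated SE of 0.175.

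**The case against.** The strongest reply is that the Analytical plan is one condensed sentence and need not be the full covariate list. The Control variables section promises adjustments that this sentence also omits, and its list is offered as examples only. Randomization describes covariates as baseline characteristics, so adjustment for baseline could be meant to include sex and age. This part stands: a reader might infer that the trial has decided to leave sex and age out, and the documents do not say so. They do set out specific fixed effects without committing to either factor, and the natural reading of the baseline term is the baseline value of the outcome. Naming the two factors removes the doubt, and does so before any imbalance is seen.

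Three stronger readings are tempting, and the documents do not support them.

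- A reader might infer that ignoring the strata makes the standard errors too large for the design. That follows when allocation is restricted within strata. The protocol specifies simple randomisation, so it does not arise.
- A reader might infer a biased estimate or a raised type I error. Randomisation protects both, and the simulation shows neither. Chance imbalance is already reflected in the standard error.
- A reader might take the gain to be large. That needs substantial sex and age effects to remain after baseline adjustment, and the documents give no source for them. Puberty state, one of the listed control variables, also overlaps with age.

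It is also fair to say that the 63 per arm belongs to AdjBMI, where little would be gained. The article does not say whether FEEL-KJ enters as raw or normed scores, although it notes that norms exist.

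**Conclusion.** The point holds as a modest one about efficiency. The trial stratifies by two factors that it calls important, uses an allocation method that does not balance them, and states a model that does not name them. The consequences are some lost precision and chance imbalance left uncorrected.

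On an assumed residual R² of 2–15%, including sex and age lifts power for a 0.5 SD effect at 63 per arm from about 80% to 81–86%. Once the baseline score is allowed for, the lower part of that range is the more plausible, and with small effects the gain is close to nil. These figures assume SD = 1, a two-sided .05 test and a single follow-up comparison.

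The point applies mainly to outcomes not stated to be age- and sex-standardised: ERSQ, DEBQ, SEES/SSES, RSA, LFPQ, CSRQ, CDI, and FEEL-KJ if raw scores are used. It applies less to AdjBMI and the waist z-scores.

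**What to change.** In the Analytical plan, specify the fixed effects as condition, time, condition by time, the baseline value of the outcome, sex, and age at the start of inpatient treatment, for all primary and secondary outcomes. Age can enter as one continuous linear term. Using the same terms for AdjBMI and waist keeps one model across outcomes and does no harm there.

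The cost is one line of text and two degrees of freedom. Sex and age must be known for every child to assign the stratum, so no new data are needed and no child is lost from the analysis. The change should be recorded before outcome data are examined by arm.

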## Discussion

The current RCT study emphasizes the growing problem of obesity, which is bidirectionally associated with the occurrence of stress (see Fig. 1) by three processes: (1) cortisol hypersecretion, (2) low-grade inflammation, and (3) emotional eating. A lack of emotion regulation competencies is hypothesized as an important intermediate factor. Therefore, the current RCT study aims to examine the effectiveness of ER Training on top of a Multidisciplinary Obesity Treatment (care as usual) in inpatient-treated youngsters (10–14 years old). The ER Training “EuREKA” is an innovative intervention program for children and adolescents, based on the evidence-based ART for adults developed by Berking and Whitley [18]. Previously, in this age group, we first tested the program in schools and designed a feasibility study in obese youngsters [147]. We hypothesize that EuREKA in addition to the MOT will result in 1) an improvement in ER competencies, more specifically having more adaptive emotion regulation strategies; 2) less emotional eating behavior; 3) better sleep quality; 4) improved weight-loss and weight-loss maintenance; and 5) better long-term (6-month) psychological well-being.

Results of this RCT study will add to the scientific and clinical literature on the role of ER in the development and maintenance of pediatric obesity. These results will be important as the role of ER in the stress-obesity relationship will be explored and elucidated. Moreover, as ER is a transdiagnostic factor and thus of importance in many psychopathologies, this study will add relevant information to the broad psychology literature. An additional important contribution of the current RCT study will be the new therapeutic insights to improve the long-term effects of existing obesity treatments [4, 96]. If these first RCT results are promising, future research should replicate these effects and can set the stage for offering the training in a new format (e.g., a digital m-health tool).

A first strength of the study is the use of a rigorous design, including a care-as-usual control group (MOT), randomization of the participants and six-month follow-up measurements to evaluate the effect of the EuREKA-training in an inpatient treatment for obesity [56]. A second strength is the use of different measurement methods (questionnaires, stress paradigm, and physiological measures) and informants (youngsters and parents) at all four data collection time points (T0, T1, T2, and T3). A third strength is the well-evaluated ART model and training, which has been the basis for the development of the EuREKA training that will be used in this study [16, 18]. Fourth, including homework in the EuREKA training is an advantage since it has the potential to increase the feeling of competence of the learned competencies in the training sessions [76].

This study also has some limitations. First, the control group is passive, and we will be unable to control for several aspects such as extra attention, rewards, and homework in the intervention group in comparison with the control group. Second, practical obstacles are expected. Therefore, a feasibility study preceding the RCT study in an inpatient treatment center for obesity was conducted, and practical difficulties concerning the organization, such as planning the extra therapy during school hours, were taken into account. However, new unforeseen obstacles cannot always be avoided. Second, no double-blind paradigm can be used, as the researchers will know who belong the EuREKA training intervention group. A consequence is a possible contamination in the instructions by the researchers and the participants of the intervention condition trying to perform better (Hawthorne effect) [78]. However, this lack is common in educational research trials [78].

